## Procedures

The intervention will consist of providing multiple HIV self-tests to women attending an ANC or post-partum clinic (PPC) in the city of Kisumu and its environs, providing information to them on how to use the self-tests and where to go for confirmatory testing and care if necessary, and then encouraging them totalk to their partner about self-testing and ask their partner to use the self-test (either independently or together).

The effect of this strategy on uptake of HIV testing among male partners will be compared with the current standard of care in which women are encouraged to refer their partner for HTC. After a 3 month period, we will obtain information from the women on the receptivity of their sexual partner to self-testing, whether they were able to use self-tests with their partner jointly or independently, and the incidence of any adverse events; participants will be encouraged to report any adverse event as soon as it occurs. Uptake of partnerHIV testing will be compared between self-testing and provider-based testing. We will also record whether the women’s partners seek confirmatory testing and link to care if an HIV-positive test result is reported to be obtained.

**Baseline data collection**

After determining that women meet the above eligibility criteria, trained RAs will obtain informed consent and then administer a baseline questionnaire,educate participants on how to use HIV self-tests (as discussed in Section I), and then give each participanttwo HIV self-tests. This will be conducted in a private location within each health facility.

In the baseline interview, we will collect data on demographic characteristics, employment, income, sexual behavior history, bargaining power in the couple, self-efficacy measures, HIV/STI testing history, partnership history, and IPV history. The purpose of the interview will be to obtain basic demographic and socio-economic information, sexual behavioral history, and history of HIV testing. Trained RAs will administer questionnaires using encrypted, password-protected tablet computers that contain forms developed using Open Data Kit (ODK), an open-access data collection platform that we have used in other studies.

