### Primary Outcome Measures

The primary outcome for the study will be uptake of HIV testing by women’s partnerswithin 3 months of enrollment in the study. For each participant, we will record whether the participant’s partner underwent HIV testing – in the case of the intervention group, this will be a report by female study participants that their partner used a self-test; in the control group, this will be uptake of HTC at the VCT by the partner. We will test for differences in the primary outcome variable between the intervention and control group.

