# STUDY DESIGN

## Overview of study design

To determine the impact of the intervention on partner or couples HIV testing, the project will use a randomized controlled trial design.

We will recruit about 600 adult womenfrom antenatal and postpartum careclinics. Participants will be randomized to one of two groups: intervention or control.

Following a baseline interview, participants in the intervention groupwill be shownhow to correctly use theself-tests and given two HIV self-tests. Subsequently, we will contact participants periodically over a 3 month period to see if they have used the test(s) with their sexual partners and conduct a follow-up interview.

Following the baseline interview, participants in the control group will be given referral vouchers for themselves and their partners to obtain HIV testing at VCT centers. We will contact the participants at the end of 3 months to see if they and/or their partner(s) have sought HIV testing.

We will also conduct in-depth qualitative interviews with a subset of study participants in the intervention group, including participants who have used HIV self-tests together with their partner, those who have used the test [partner testing] and those who have not used HIV self-tests.

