**Randomization**

Following completion of the interview, each participant will be randomly assignedto one of the two study arms.We will conduct 1:1randomization in blocks of 20 study participants so that an equal number of participants will be randomized to the control group and intervention group. The group to which each participant is assigned will be recorded by the RAs and linked to the participant’s study ID number.

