**Intervention group**

Participants in the intervention group will be given clear, accessible instructions on how to use the tests (this will be communicated to them and provided on a written document). Participants will be instructed to call a phone hotline that we will establish in the event of any adverse events that they or their sexual partners experience. They willalso be given a list of places that partners can access for confirmatory testing and advisedto encourage their partner to go for confirmatory testing.

They will be also receive information about HIV self-testing including reasons for suggesting usage of the self-test to their partner and strategies for introducing self-tests to their partners; however, it will also be emphasized that women are under no obligation to suggest to their partner or convince him to use the self-test. Because use of self-tests at home will mean that a trained counselor will not be present when women or their partners take the test, we will develop messages that can be communicated to women easily so that they and their partners can use the self-tests correctly and safely on their own. The messages and counseling that we will provide will adhere to Kenya’s National Guidelines for HIV Testing and Counseling [16].

Two self-test kits will then be distributed to women, each containing the following:

- One standard OraQuick ADVANCE I/II test kit with developer fluid vial and stand;
- Written pre-test information including test instructions in written and pictorial form, post-test counselling information and details about how and where to access HIV confirmatory testing in or near Kisumu;
- Aphone number that participants can call to obtain additional information about taking the test, interpreting results, obtaining referral information,post-test counseling or obtain help in case of IPV.
- Two voucherswith unique identifying numbers which can be redeemed at confirmatory testing for a small token.

All the information above will be communicated orally to women initially and also provided in written form ofan information sheet, in English, Kiswahili and Luo.

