**Control Group**

The control group will get standard of care ante/post-natal care as per the MoH guidelines whereby pregnantwomen are encouraged to learn their HIV infection status, as well as that of their sexual partners.For postnatal women, HIV counseling and testing is usually offered to all women with unknown HIV status. In the study, all women in the control group will be given referral coupons with unique identifying numbers which they (and their partners) can redeem at a VCT center for a small token. Participants will be encouraged to go to one of the study facilities for HIV testing.

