## Potential risks of proposed research to study participants

We anticipate minimal risks to study participants. Although there is a potential for exposing a participant’s personal information to others during the interview, every consideration will be taken to ensure the interview is conducted in a private place. Study procedures will be thoroughly explained to participants and they will be consented only if they fully understand study procedures and find them acceptable. Participants are allowed to exit from the study at any time.

We do not anticipate any adverse events following the self-testing, outside normal reactions similar to those occurring among persons testing for HIV the first time.These may include negative reactions to an HIV diagnosis or incorrect test results. Participants will be advised to visit a voluntary counseling and testing (VCT)clinic for a confirmatory test as the self-test is a primarily a screening test. The participants will be well trained on self-testing and counseled before being given the test kits. They will also be given a phone number they can call at any time.The information given will instruct the participants about the potential benefits to using the test prior to sex with a partner (for example, knowing partner’s status before sex can lead to better risk reduction). They will also practice and become comfortable using the kits during this session. All of this will take place at the time of enrollment.

There is a risk that sexual partners will react adversely to the participants’suggestions of self-test usage or to the test result itself. To minimize this risk, we will provide detailed information on the need for confirmatory testing and the availability of HIV care and treatment for HIV-infected persons. We will not enroll women who self-report concern that their partner may hurt them if they suggest using the HIV self-test and in addition we will refer men and women who experience violence forto IPV services.

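### The baseline instructions give every participant self-test training and two kits with no arm named, contradicting the sections that reserve both for the intervention group

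*Protocol*

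**What the plan says.** Under Procedures, Baseline data collection lists what research assistants do once a woman is found eligible: obtain consent, administer the questionnaire, then "educate participants on how to use HIV self-tests (as discussed in Section I), and then give each participanttwo HIV self-tests". The cross-reference to a Section I matches nothing in the numbered table of contents.

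The next section, Randomization, states: "Following completion of the interview, each participant will be randomly assignedto one of the two study arms".

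Other sections assign the same steps by arm:

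- Overview of study design says that, after the baseline interview, "participants in the intervention groupwill be shownhow to correctly use theself-tests and given two HIV self-tests", while "participants in the control group will be given referral vouchers for themselves and their partners to obtain HIV testing at VCT centers".
- Study population says that half the women at each site receive the intervention and the other half the standard of care.
- Intervention group covers instruction first and then states: "Two self-test kits will then be distributed to women, each containing the following".
- Control Group describes standard ante- or postnatal care and adds that "all women in the control group will be given referral coupons with unique identifying numbers".

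Potential risks of proposed research to study participants describes training at enrolment, again with no arm named: "They will also practice and become comfortable using the kits during this session".

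The primary outcome is defined differently by arm. In the intervention group it is the woman's report that her partner used a self-test. Primary Outcome Measures then says "in the control group, this will be uptake of HTC at the VCT by the partner". Statistical analysis repeats this split. Limitations adds a self-report, the same in both arms, of partner testing by any modality.

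**The concern.** Kits and the training that goes with them are the whole randomised contrast. Baseline data collection is the section staff would consult at the enrolment visit, and its wording covers every woman enrolled. The Randomization section uses the same unqualified term for everyone who is allocated, so on a plain reading the kit instruction includes controls.

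If it were followed, control women would be treated, and the arm-specific outcome definition would make the damage hard to see. A self-test used by a control partner does not meet the control definition of the primary outcome. The primary comparison would then reflect which kind of test is counted in which arm, not whether the woman was given kits.

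**Working it through.** **1. The sections side by side**

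| Section | Who is trained and given kits | Timing |
|---|---|---|
| Baseline data collection | Each participant, no arm named | After the questionnaire; section precedes Randomization |
| Randomization | Not addressed | Allocation after the interview |
| Overview of study design | Intervention group; controls get vouchers | After the baseline interview |
| Study population | Half of each site gets the intervention, half standard care | Not stated |
| Intervention group | Intervention group | Section follows Randomization |
| Control Group | Controls get standard care and coupons | Section follows Randomization |

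The first row cannot be followed together with the third, fourth and sixth. The conflict over who gets kits is explicit. The conflict over timing is weaker: Randomization ties allocation to the end of the interview, not to the hand-out of kits, so the idea that kits come before allocation rests on section order.

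**2. The plan's own figure**

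Inputs from Sample size justification: 20% versus 30%, 300 per group, 80% power. Two-sided 0.05 is assumed, because Statistical analysis states it only for the other tests. No value is given for the design effect, so 1.0 is used.

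With p̄ = (p1 + p2)/2, a pooled null variance and no continuity correction:

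n = [1.96·√(2p̄(1−p̄)) + 0.842·√(p1(1−p1) + p2(1−p2))]² / (p2−p1)²

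= [1.96·√0.375 + 0.842·√0.37]² / 0.01 = 294 per group after rounding up.

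Power = Φ{[(p2−p1) − 1.96·√(2p̄(1−p̄)/n)] / √([p1(1−p1) + p2(1−p2)]/n)}

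At n = 300: Φ[(0.10 − 0.0693)/0.0351] = 80.9%. The stated 300 and 80% reproduce on these settings. With a continuity correction the figures are 313 per group and 78.2% power at 300.

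**3. Primary outcome if controls received kits**

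Control self-tests are not counted, so the recorded control rate does not rise because of them. As an illustrative extreme, suppose every control woman has kits and partners in both arms test at 30% by any modality. The true difference is 30 − 30 = 0 points. Suppose also that self-tests prompt no extra VCT visits. The recorded difference is then 30 − 20 = 10 points if control clinic attendance is unchanged, and 30 − 0 = 30 points if self-tests replace every clinic visit. If control partners went on to a VCT after self-testing, the recorded control rate could rise instead. The documents give nothing to fix the direction or size, only that the estimate would be biased.

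**4. Any-modality self-report if controls received kits**

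Here control self-tests do count. Assume the planning rates of 20% and 30% also apply to this outcome, and that a fraction c of control women get kits and their partners test at 30%. The control rate is 0.20 + 0.10c. With 300 per arm and the power formula above:

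| c | Control rate | Power |
|---|---|---|
| 0 | 20% | 80.9% |
| 10% | 21% | 71.6% |
| 20% | 22% | 60.8% |
| 30% | 23% | 49.3% |

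The protocol gives no leakage rate; every non-zero value of c is an assumption.

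**The case against.** The strongest reply is that the intended design is not in doubt. The Abstract, Overview of study design, Study population, Intervention group and Control Group all point the same way, and arm-specific instructions follow directly after the baseline section. One unqualified clause stands against all of them. This is right as to intent: a reader might infer that the trial plans to give kits to controls, and the protocol does not support that. It does not remove the defect, because the clause is an instruction to staff and conflicts with the others as written.

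A reader might also infer that kits are definitely handed out before allocation. That goes further than the text. The order interview, allocation, kits fits Overview of study design, Randomization and Intervention group. Whatever the order, the wording still includes controls.

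The risk section is weak support. It describes women who will be given kits and sets no order relative to allocation, so it is not a second instruction to treat both arms. It needs an arm qualifier only for consistency.

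Finally, it is tempting to say that the primary contrast would fall to zero, or that primary power would fall to 72%, 61% or 49%. The outcome definition rules this out, since only VCT testing counts in controls. Those figures apply to the any-modality self-report. That self-report would also bring some control kit use to light, so contamination would not be wholly hidden, though it would show only at follow-up and outside the primary outcome.

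**Conclusion.** The concern holds as an internal contradiction, probably a drafting error, in an operational section used at three facilities. It is not evidence of a flawed design, and harm follows only if staff act on the clause as written. In that case control women would receive the intervention and the primary estimate would be biased by an amount and in a direction the documents do not determine. The any-modality comparison would be diluted towards no difference. The power loss for that comparison, from 81% to 72%, 61% or 49%, rests on assumed leakage of 10%, 20% or 30%, on the 20% and 30% planning rates carrying over to that outcome, on two-sided 0.05 and on no design effect. The contradiction itself depends on none of these figures. It should be corrected before enrolment, because the clause bears directly on the randomised contrast and is cheap to change.

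**What to change.** Reconcile Baseline data collection with Overview of study design, Randomization, Intervention group and Control Group. End the baseline paragraph at the questionnaire and remove or correct the reference to Section I. State that randomisation comes next. Then have the arm-specific steps carried out only in the arm that Overview of study design, Intervention group and Control Group already name: instruction and kits in one, referral vouchers in the other. Add the arm to the description of kit training in the risk section, and bring any site procedures into line.

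The cost is about one paragraph of wording. The sample size and the analysis do not change. A log of kits issued by study ID and arm would let adherence be checked, but it is optional and not needed to resolve the contradiction.

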**Randomization**

Following completion of the interview, each participant will be randomly assignedto one of the two study arms.We will conduct 1:1randomization in blocks of 20 study participants so that an equal number of participants will be randomized to the control group and intervention group. The group to which each participant is assigned will be recorded by the RAs and linked to the participant’s study ID number.

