## Exclusion criteria

Participants who meet the following criteria will notbe eligible for enrollment:

1. Male
2. Age <18years or >39years
3. Believes that her partner will hurt her if she gives him an HIV self-test and encourages him to use it
4. Reports having an HIV+ partner
5. Intends to relocate from Kisumu area within the next 3 months

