## Sampling

Research Assistants (RAs) will invite eligible individuals to participate in the study.Recruitment of participants will take place at the Lumumba Health Centre in Kisumu, Kisumu East District Hospital and Rabuor Health center. Staff at the ANC and PPC clinics will inform patients as they are being discharged home that there is a study they may qualify for; if they express interest in learning more, they will be given a referral coupon to take to the study staff based at the facility. For ANC and PPC patients, the referral coupons will be identical and will have a unique number rather than the women’s names or any other identifying information. Before issuing the coupon to women, the ANC and PPC staff will write down a discreet code for whether the woman is HIV-positive or HIV-negative (OP for HIV-positive and ON for HIV-negative). Only the study and clinic staff will know what the codes denote. We believe the coding system will be discreet enough to not disclose the HIV status to unauthorized person(s). This information will be necessary for assessing participation rates in the study by HIV-positive and HIV-negative women, analyzing use of self-testing by HIV status, and for sampling HIV-positive and HIV-negative participants in qualitative interviews. Once the RAs collect the referral coupons from the women, the number on the coupon and the HIV status code on the coupon will be recorded on secure tablets. No identifying information will be collected for women who decline to participate in the study.

Women at all stages of pregnancy and post-partum care will be referred to study RAs. The study RAs will then explain the study to women, screen them for eligibility for the study, and ask those who are eligible if they are willing to participate in the study. RAs will obtain informed consent and enroll the woman into the study. We will conduct recruitment in the study facilities in a manner that ensures the number of participants in each facility is proportional to the number of women who seek care at each facility.

During the qualitative phase of the study, we will purposively sample a sub-set of about 45 study participants. We will seek to include 10-15 women who tested together with their partners (couples testing), 10-15 women who gave the test to their partner to use (partner testing), and 10-15 women who never used the test or gave it to their partner to use.We will sample from among all study sites and both ANC and PPC clients.

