# ETHICAL CONSIDERATIONS

## Informed Consent

Before studyenrollment, womenwill be introduced to the study and its aims, as outlined in the informed consent document. The consent forms will describe the study procedure in the language (English, Swahili or Dholuo) preferred by the participant. The subject will be asked to read and review the document. Interviewers will be careful to impress upon subjects that they may choose to decline participation or withdraw from the study at any time. Those who agree to participate in the study will be asked to sign and date the informed consent form prior to enrollment and random assignment. If a subject cannot read, the consent form will be read to them and oral consent will be obtained,with a witness providing his or her signature. A copy of the informed consent document will be given to the subjects for their records.

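### One disclosed, fixed block size of 20 in an open trial: if blocks run within site and the site team sees every assignment, the last place in each block is known in advance

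*Protocol*

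**What the plan says.** The Randomization section fixes 1:1 allocation "in blocks of 20 study participants so that an equal number of participants will be randomized" to each arm, so each complete block holds 10 women per arm. Assignment follows the baseline interview, and "The group to which each participant is assigned will be recorded by the RAs". Informed Consent has women "sign and date the informed consent form prior to enrollment and random assignment".

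RAs carry out every step before that. Under Sampling they "screen them for eligibility for the study, and ask those who are eligible if they are willing to participate", and "RAs will obtain informed consent and enroll the woman into the study". Under Baseline data collection, "trained RAs will obtain informed consent and then administer a baseline questionnaire".

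The arms look different to staff: two self-test kits in one (Intervention group), referral coupons without kits in the other (Control Group). Study population promises an even split of women between the arms at each site. The Randomization section does not say whether blocks run within site or on one list for all three facilities.

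One exclusion criterion rests on what the woman tells the RA: "Believes that her partner will hurt her if she gives him an HIV self-test and encourages him to use it".

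**The concern.** Someone who sees each assignment and knows the block size can count. Once one arm has reached 10, every remaining place in that block belongs to the other arm. The prediction comes from earlier assignments, so it is available before the next woman has been screened or consented.

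That matters because screening depends partly on what the RA draws out. Fear of partner violence, having a primary partner and intention to stay in the area are all elicited in conversation. An RA who expects a kit assignment may, without intending it, probe fear of violence harder than one who expects a coupon assignment. The arms would then differ in how cooperative the partners are, which bears on the primary outcome, and in baseline risk of violence, which bears on the main harm. The adjusted model under Statistical analysis covers age, education, clinic type and partner age, education and employment. It includes neither violence history nor bargaining power in the couple, so it would not remove such a difference.

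**Working it through.** **Plan's own figures.** The protocol gives no figure for predictability. The yardstick is its planned difference of 20% versus 30% with 300 women per arm and 80% power (Sample size justification). I assume two-sided alpha 0.05 for the primary test, since the text attaches that level to the other tests.

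- n = [1.96·√(2×0.25×0.75) + 0.8416·√(0.20×0.80 + 0.30×0.70)]² / 0.10² = (1.200 + 0.512)² / 0.01, which gives 294 per arm without continuity correction (313 with it).
- Power at 300 per arm is 80.9% without the correction and 78.2% with it. The stated 300 and 80% are reproduced by the uncorrected form.

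**Inputs for predictability.** Block size 20 and m = 10 per arm (Randomization); N = 600, which is 30 blocks. Assumption: the observer sees every earlier assignment in the block and knows where the block began.

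**Forced places.** The last k places all fall to one arm with probability 2·C(20−k, 10)/C(20, 10):

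| k | Probability |
|---|---|
| 1 | 100% |
| 2 | 47.4% |
| 3 | 21.1% |
| 4 | 8.7% |

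The expected number of forced places is 2m/(m+1) = 20/11 = 1.82 per block. As a share, 1.82/20 = 9.1%. Over 30 blocks, 30 × 1.818 = 54.5, about 55 of 600.

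**Best guess throughout the block.** Always guessing the arm that is behind gives m + (4^m/C(2m, m) − 1)/2 correct guesses = 10 + (1,048,576/184,756 − 1)/2 = 12.34 of 20, or 61.7%, against 50% by chance. By simulation, about 27% of places have odds of 2:1 or better for one arm.

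**If one list serves all sites.** I took site shares from the monthly antenatal plus postpartum counts under Study site: 460, 880 and 310 of 1,650. With RAs seeing only their own site, the simulated hit rate is about 54%, even when block boundaries are known.

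**Possible effect on the result.** About 54.5/2 = 27 places per arm are forced, which is 9.1% of 300. Suppose steering made women in the forced places differ between arms by 20 points in partner testing (an assumption; the protocol gives no such figure). The estimated difference would shift by 0.091 × 20 = 1.8 points. For an assumed 10 to 30 points, the shift is 0.9 to 2.7 points. Steering on guesses short of certainty could add to this and is not counted.

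**Alternative block sizes.** Hit rate for guessing the arm that is behind:

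| Blocks | Hit rate |
|---|---|
| Fixed 4 | 70.8% |
| Fixed 8 | 66.6% |
| Fixed 20 | 61.7% |
| Varied 4/6/8 | about 68% |
| Varied 8/10/12 | about 65% |
| Varied 16/20/24 | about 61.7% |

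Varying the size near 20 leaves the hit rate where it is. It hides where a block ends, so the count alone no longer makes the last places certain. Small blocks make guessing easier.

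**The case against.** The case for leaving the text alone has substance.

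- **A block of 20 is large.** It is harder to guess than fixed blocks of 4 or 8. This stands, and it is why the fix must not shrink the blocks.
- **Assignment comes after consent and the baseline interview.** This limits steering once a woman has been screened. It does not reach the screening conversation itself.
- **Screening leaves a trail.** There is a screening questionnaire (Appendix 1), clinic staff make the first referral with numbered coupons logged on tablets (Sampling), and reasons for ineligibility are tabulated (Data management). Unusual use of the violence exclusion might therefore be noticed. A plain tabulation, however, would not show whether it was used more often when a kit assignment was due.
- **Imbalance could be examined.** Violence history, bargaining power and testing history are collected before assignment. This helps detection, not prevention.
- **Predictability is not bias.** The protocol gives no evidence that anyone would steer. This stands and keeps the severity low.
- **Who generates and holds the list is operational detail.** That silence may be filled elsewhere and is not counted here. The point concerns the fixed size that the protocol does state.

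A reader might infer that the end of every block is predictable in this trial as written. The protocol does not establish that, because it depends on within-site blocks and on a team that sees every assignment. A reader might also infer that one person screens, enrols and records the arm. The text names a role, not an individual.

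**Conclusion.** The point holds conditionally and is of low severity. The protocol states and discloses one fixed block size in an open trial whose recruiting staff also record the arm. With within-site blocks and full visibility, 9.1% of assignments are known in advance, at a time when eligibility is still being elicited. The even split promised at each site makes within-site blocks the more natural reading, but they are not stated. Under a shared list with site-only visibility, most of the problem disappears.

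The bias of roughly 2 points rests on an assumed 20-point difference and on steering in all forced places. It would not by itself account for a 10-point effect. The documents do not support saying that the arms will be unbalanced or that the primary comparison is unsound.

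**What to change.** In the Randomization section:

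1. Replace the fixed block of 20 with permuted blocks whose sizes vary at random and stay near 20, for example 16, 20 and 24. Do not use small blocks.
2. Keep the sizes out of the protocol copy and any other document the RAs hold.
3. State that blocks run within site, in line with the even split promised under Study population.
4. State that each arm is released only after eligibility, consent and the baseline form are complete and locked.

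The cost is a new allocation list and a rule for when the arm is released, with no extra participants or visits. The existing tablet forms could serve for the release, but the protocol describes them only for questionnaires, so that would need checking. The statistical price is a possible final imbalance of a few women per site where the last block is unfinished. The change takes away certainty at the end of a block; it does not bring the guess rate below about 62%, and the protocol should not claim that it does.
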